## Abstract

**Introduction:**

The use of risk functions to individualize preventive interventions is a key strategy in the primary prevention of coronary heart diseases (CHD). Unfortunately, most risk functions still fail to identify many individuals who will experience a cardiovascular (CV) event. Detecting individuals with asymptomatic peripheral artery disease (PAD) with a new risk function could improve CV risk classification. The aim is to evaluate the effectiveness of integrating an ankle-brachial index (ABI) program into the current CHD risk detection strategy to identify populations at high risk of asymptomatic PAD, reducing the incidence of CHD and mortality in those aged 50 to 74 years.

**Methods:**

This study is a pragmatic randomized cluster trial. A total of 274 primary care centers will be randomized into two groups that will either maintain the current CHD risk detection strategy or add a screening program to detect asymptomatic PAD using ABI. In routine clinical practice, 10-year CHD and PAD risk are assessed using the Framingham-adapted (REGICOR) function and the REASON function, respectively. The study population will consist of patients aged 50 to 74 years with a CHD risk ≥ 7% and PAD risk ≥ 7%, making them candidates for an ABI measurement. Cases with an ABI result ≤ 0.9 will have their CHD reclassified as high or very high by doubling the initial REGICOR score and receive the recommendations of the lipid and cardiovascular risk guideline. The primary outcomes will be hard CHD, major adverse cardiovascular events (MACE), all-cause mortality, and improvement in CVD risk factors. Secondary outcomes include CHD (a composite of angina and hard CHD), cerebrovascular disease, and adverse effects from lipid-lowering medication. Survival analysis will estimate the effectiveness of adding the ABI screening strategy, with Cox models (intention-to-treat) and marginal structural models controlling for confounding variables.

**Results and discussion:**

Direct health improvements in the intervened population are expected, including a reduction in CHD incidence and its risk factors. This project is particularly valuable, as delays in screenings and control of CV risk factors have accumulated after the COVID-19 pandemic. Therefore, this work is expected to help recover and enhance cardiovascular risk prevention efforts.

**Clinical trial registration:**

ClinicalTrials.gov, NCT05884840.

## Introduction

1

Mortality due to cardiovascular diseases (CVD) in Spain accounted for 26.4% of all deaths in 2021; 28.9% of those occurred in women and 24.2% in men, and 24.2% were related to ischemic heart disease (1). Moreover, CVD also poses a huge economic burden: in 2021, the total cost of CVD was estimated to be €282 billion, 11% of EU-health expenditure (2).

The use of risk functions to individualize preventive interventions is a key strategy in primary prevention for CVD (3). The current coronary heart disease (CHD) screening risk function in some regions of Spain is the Framingham-adapted REGICOR (*Registre Gironí del Cor*) function (4). This function is integrated in the primary care electronic health records (EHR) system and predicts the probability of developing a coronary event within 10 years (5). Those with more than 10% of such probability are at high-risk, and thus, candidates for treatment with lipid-lowering medication and recommendations on healthy lifestyles. However, studies have also described that many events occur in people classified as having moderate risk (5–9.9%), who are not yet candidates for treatment (5, 6).

The current primary prevention strategy proposes additional (bio)markers to improve CHD risk classification (7, 8). A good CHD (bio)marker meets some basic criteria: (a) it is easily measurable and has a relatively high prevalence, (b) it is an independent predictor of CHD, and (c) when evaluated, it should classify a substantial proportion of the population who will suffer cardiovascular (CV) events as being at high risk (9). Among these (bio)markers, those that identify the presence of asymptomatic atherosclerosis are the most reliable to detect patients in the highest risk group (3, 9, 10).

The ankle-brachial index (ABI) is one of the best candidates that meet the above-mentioned three criteria (7, 8). The ABI can be easily measured with a non-invasive and inexpensive technique. Values lower than 0.9 are used to diagnose lower extremity artery disease [henceforth referred to as peripheral artery disease (PAD), which is associated with higher mortality risk and CV events (11)]. The ABI values provide independent risk information additional to coronary risk functions (7). A meta-analysis showed that having an ABI below 0.9 doubled the 10-year total mortality, CV mortality, and the risk of a major coronary event (MACE) (7). As noted by Poredoš et al., a low ABI is a useful screening tool that can be helpful in re-classifying patients’ CV risk into higher categories (12). Furthermore, a more recent local study performed in the province of Barcelona, the ARTPER study, also reported that the presence of PAD doubles, at a minimum, the risk of MACE as well as the risk of coronary disease and vascular mortality (9). Importantly, another local study in Girona (a region of Catalunya) reported that 86% of people with an ABI ≤ 0.9 did not exhibit any symptom (13).

Even though the ABI test is a simple technique and is performed regularly in the primary care settings, it is also time-consuming and requires devices and trained personnel to ensure accurate measurements (13). The inter-society consensus (ISC) practice guidelines for the management of people with PAD recommend ABI screening in patients aged 50–70 who have diabetes or are smokers, and in patients older than 70 years (14). However, these recommendations have a limited level of evidence, and the precision of PAD detection in the asymptomatic population has been hardly studied.

Therefore, we designed a new risk function, derivation of the REgicor and Artper Score fOr aNkle brachial index screening (REASON) (15), to select the best candidates for an ABI measurement. This model improved the prediction of ABI ≤ 0.9 in Spanish patients aged 50–74 who were apparently free of CHD (16), and showed similar sensitivity and improved specificity compared to ISC. Furthermore, the predictive ability of REASON can be modulated by changing the cut-off risk point. This feature can be useful to manage the available resources for CV prevention in each region of the world (15). A cut-off point of 7% has a sensitivity of 68%, a specificity of 72%, and selects 35% of the population as candidates for ABI screening (15). This improvement in predictive capacity translates into a considerable reduction in the number of screened people needed to detect a case with ABI ≤ 0.9. Therefore, by reducing the number of false positives and maintaining the sensitivity, the use of REASON should limit the workload and possible adverse events associated with CHD diagnostic procedures and medical treatments (15).

The adoption of a strategy that combines the current CHD risk estimation with REGICOR and the probability of having an ABI ≤ 0.9 assessed with REASON would detect patients that require an ABI test and improve the CHD risk classification (7, 8, 17). The diagnosis of asymptomatic PAD at an early stage can be a critical opportunity to influence the disease progression, prevent its complications, and control its risk factors. Additionally, early diagnosis can also be a motivation to help patients accept the recommendations and improve lifestyle habits, such as smoking cessation, diet, and increased physical activity.

The study that measured the predictive capacity of REASON for ABI ≤ 0.9 was observational, and thus, further research is needed to validate its results (15). Consequently, we have designed this clinical trial to appraise the effectiveness of REASON:

The aims of this study are: (1) to evaluate the effectiveness of integrating an ABI screening program into the current CHD risk assessment strategy for reducing the incidence of CHD and all-cause mortality among individuals aged 50 to 74, and (2) to evaluate the effectiveness of integrating an ABI screening program into the current CHD risk assessment strategy for mitigating CV risk factors among individuals aged 50 to 74.

## Methods

2

### Study design

2.1

This study will be conducted as a pragmatic cluster randomized trial in the primary care centers (PCC) of Catalonia. Patient monitoring will take place during a period of 2 years (2023–2025).

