### Sample size

2.3

The incidence of CV events (coronary or cerebrovascular disease, or symptomatic PAD) is expected to be 7% in the selected population during a period of 3 years. Accepting a 0.05 alpha risk and a 0.2 beta risk in a bilateral contrast, 20,171 people are needed in each arm, intervention and control groups, to detect a relative risk of 0.9.

Around 500.000 people aged 50–74 years have their CHD risk calculated in Catalonia per year. Out of those, we estimate that 36.000 will present both a REGICOR and REASON score ≥ 7%. Thus, in one and a half years we expect that there will be 54.000 people, 27.000 for each arm.

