#### Monitoring and result variables

2.5.2

Monitoring of the patients’ data will occur every 3 months during the first semester of the study to assess the implementation. After that, it will be conducted every 6 months up to 3 years from the patients’ study enrolment.

The study primary outcomes will be hard CHD (myocardial infarction, cardiac revascularization, or coronary death); major adverse cardiovascular events (MACE), a composite of hard CHD and stroke (fatal and nonfatal ischemic stroke); all-cause mortality; and variables related to the assessment of CVD risk factors improvement: tobacco consumption, lipid profile, systolic and diastolic pressure, weight, height, body-mass index (BMI), glycemia, glycated hemoglobin (in patients with DM), creatinine, proteinuria, albumin-to-creatinine ratio, and glomerular filtration rate.

The secondary outcomes will be CHD (a composite of angina and hard CHD), cerebrovascular disease (a composite of stroke [fatal and nonfatal ischemic stroke] and transient ischemic attack); CVD (a composite of MACE, angina, and transient ischemic attack); lipid lowering medication adverse effects: short-term effects (muscular and hepatic alterations) and long-term effects (diabetes and cancer).

The considered potential confounding variables included sociodemographic information: age and sex; PHC related variables: attendance rate, billing rate, and length of time in the EHR; alcohol consumption; comorbidities: diabetes, atrial fibrillation, heart failure, dementia, endocrine and metabolic conditions, inflammatory diseases, asthma, chronic obstructive pulmonary disease, depression, CVD incidence rate; other comorbidities identified in the bivariant analysis; used medication: corticosteroids, antidepressants, hormonal substitutive therapy, oral contraceptives, antipsychotics, anti-inflammatories, Platelet aggregation inhibitors (other than heparin), antihypertensives, anti-diabetic drugs, and lipid lowering medication; laboratory related variables: alanine transaminase (ALT) and aspartate aminotransferase (AST). We will also record health-care quality standards of health care providers and a deprivation index (MEDEA index) (16).

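### Section 2.1 sets 2 years of patient monitoring (2023–2025), but sections 2.3 and 2.5.2 rest on 3 years per patient; the data cut and the power depend on which holds

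*Protocol article*

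**What the plan says.** Three sections of the protocol article bear on the length of follow-up.

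- **Section 2.1, Study design:** "Patient monitoring will take place during a period of 2 years (2023–2025"). It does not say whether the 2 years are a calendar window or time per patient.
- **Section 2.5.2, Monitoring and result variables:** after a first semester with three-monthly monitoring, "After that, it will be conducted every 6 months up to 3 years from the patients’ study enrolment". This clock starts at each patient's own enrolment.
- **Section 2.3, Sample size:** the event risk (coronary or cerebrovascular disease, or symptomatic PAD) "is expected to be 7% in the selected population during a period of 3 years". From that risk, "20,171 people are needed in each arm, intervention and control groups", "to detect a relative risk of 0.9". On feasibility, "in one and a half years we expect that there will be 54.000 people", that is, 27,000 per arm.

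**The concern.** Sections 2.1 and 2.5.2 both describe monitoring of patients, so they cannot be read as covering different activities. Recruitment over 1.5 years followed by 3 years for the last patient ends about 1.5 + 3 = 4.5 years after the start. That does not fit into 2023–2025 on any reading.

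The follow-up rule fixes two things: the date of the data extraction and the number of events in the survival analyses of section 2.6. With two rules in print, a cut at either date could later be called protocol-compliant. If section 2.1 governs, the 3-year event risk behind the sample size will not be reached. Under a 2-year calendar window the last patients enrolled would have about six months of follow-up, in a trial whose effect must work through ABI testing, reclassification, treatment and lifestyle change.

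**Working it through.** **Inputs from section 2.3.** Control risk p1 = 0.07 over 3 years; relative risk 0.9, so p2 = 0.9 × 0.07 = 0.063; two-sided alpha 0.05 (z = 1.960); power 80% (z = 0.842); 20,171 per arm needed; 27,000 per arm expected over 1.5 years.

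**Step 1: reproduce the stated sample size.** With p̄ = (0.07 + 0.063)/2 = 0.0665, the two-proportion formula is

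n = [1.960 × √(2p̄(1 − p̄)) + 0.842 × √(p1(1 − p1) + p2(1 − p2))]² / (p1 − p2)² = 19,887 (rounded up).

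The continuity correction, n/4 × [1 + √(1 + 4/(n × 0.007))]², gives 20,171, an exact match. The stated number therefore rests on the 3-year risk. Expected events are 20,171 × (0.07 + 0.063) = 2,683, or 27,000 × 0.133 = 3,591 at the expected recruitment.

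**Step 2: convert to shorter follow-up.** The article gives no event-time distribution, so I assume constant hazards that meet the 3-year risks:

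- control: −ln(0.93)/3 = 0.02419 per year
- intervention: −ln(0.937)/3 = 0.02169 per year
- hazard ratio 0.897, with |ln HR| = 0.109

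Two readings keep the stated 2 years.

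- *Two years for every patient.* Risk = 1 − exp(−2λ): 4.72% and 4.25%.
- *Two-year calendar window with all recruitment inside it.* I assume uniform accrual over 1.5 years from the opening of the window, so follow-up runs from 0.5 to 2 years (mean 1.25). Average risk = 1 − [exp(−0.5λ) − exp(−2λ)]/(1.5λ): 2.97% and 2.67%.

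**Step 3: power.** With d events and equal arms, Schoenfeld's formula is power = Φ(√d/2 × 0.109 − 1.960). For the calendar window at 27,000 per arm, d = 1,524, √1,524/2 × 0.109 = 2.13, and Φ(0.17) = 57%.

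| Follow-up rule | 20,171 per arm: events, power | 27,000 per arm: events, power |
|---|---|---|
| 3 years for every patient | 2,683, 81% | 3,591, 90% |
| 2 years for every patient | 1,809, 64% | 2,421, 76–77% |
| 2-year calendar window, 18-month accrual inside | 1,138, 45% | 1,524, 57% |

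A two-proportion power calculation agrees with these figures to within about one percentage point; the range 76–77% reflects the two methods (76.4% and 76.5%).

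**Step 4: sensitivity.** If the relative risk of 0.9 is instead taken as a hazard ratio of 0.90, the calendar-window power at 27,000 per arm is 54%. If 2023–2025 is stretched to 36 calendar months with 18-month accrual, power is 69% at 20,171 per arm (2,027 events) and 81% at 27,000 (2,714 events), but that sets aside the words of section 2.1, which say 2 years.

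**The case against.** The best defence is that two sections out of three agree on 3 years. Section 2.5.2 is the detailed operational rule, with a schedule and a per-patient anchor, whereas section 2.1 is a single summary sentence. If 3 years per patient is what is meant, the sample size reproduces exactly and power is 81% to 90%. This stands: the sample-size arithmetic is not wrong on this point, and nothing shows that a short follow-up was chosen deliberately. It does not remove the conflict, because section 2.1 also names calendar years, and those cannot contain 3 years per patient.

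A reader might infer that power is at most 57% under the 2-year statement. The document does not support that as a ceiling. The 57% belongs to one reading, a calendar window with uniform accrual inside it. Section 2.1 does not say that it means a calendar window, and section 2.3 does not say that recruitment and the monitoring period start together.

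A reader might also set 1,524 expected events against 2,683 planned. Those counts come from different populations, 54,000 and 40,342 people. Like for like, the comparison is 1,524 against 3,591, or 1,138 against 2,683.

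Finally, these figures describe the composite in section 2.3. None of the primary outcomes in section 2.5.2 is that composite, so they are not the power for hard CHD, MACE or all-cause mortality.

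**Conclusion.** The contradiction is real and has to be resolved, because it decides when the data are cut and how many events are analysed. That ground suffices without any power figure.

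The size depends on the reading. Compared with 3 years for everyone, 2 years per patient lowers power for the sample-size composite from about 81% to 64% at 20,171 per arm, and from about 90% to 76–77% at 27,000. The calendar window lowers it to about 45% and 57%. Both readings that keep 2 years fall short of the planned 80%, even at full expected recruitment.

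The shorter-follow-up figures rest on constant hazards calibrated to 7% and 6.3% at 3 years and, for the calendar window, on uniform 18-month accrual. No figure allows for clustering or dropout, for which the article gives no values; positive within-centre correlation or loss to follow-up would lower them all.

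**What to change.** Use one follow-up rule throughout.

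- **Option 1: 3 years per patient.** Change section 2.1 to agree with sections 2.3 and 2.5.2: every patient is followed in the electronic health record for 3 years from enrolment, with the final extraction 3 years after the last enrolment. Section 2.3 then needs no change on this point. Because the data come from routine records, the cost is a corrected sentence and a later data cut.
- **Option 2: keep the 2025 cut.** State whether the 2 years are a calendar window or time per patient, and bring section 2.5.2 into line. In section 2.3, replace the 3-year risk of 7% with the incidence expected at the follow-up patients will actually have, and restate the power. The cost is a less favourable stated figure.

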### Participants

2.2

We will include people aged 50 to 74 years who had a REGICOR score ≥ 7% and a REASON score ≥ 7%, during a routine primary care visit. The exclusion criteria are patients with a previous history of symptomatic PAD, coronary disease, stroke, cardiac revascularization, or cLDL≥ 190 mg/dL or equivalents.

### Sample size

2.3

The incidence of CV events (coronary or cerebrovascular disease, or symptomatic PAD) is expected to be 7% in the selected population during a period of 3 years. Accepting a 0.05 alpha risk and a 0.2 beta risk in a bilateral contrast, 20,171 people are needed in each arm, intervention and control groups, to detect a relative risk of 0.9.

Around 500.000 people aged 50–74 years have their CHD risk calculated in Catalonia per year. Out of those, we estimate that 36.000 will present both a REGICOR and REASON score ≥ 7%. Thus, in one and a half years we expect that there will be 54.000 people, 27.000 for each arm.

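### The sample size rests on a composite that includes symptomatic PAD and is not a listed outcome, so the stated 80% power belongs to none of the trial's outcomes

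*Protocol article*

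**What the plan says.** Section 2.3 (Sample size) starts from one endpoint: "The incidence of CV events (coronary or cerebrovascular disease, or symptomatic PAD) is expected to be 7% in the selected population". The period is 3 years. The error rates are set by "Accepting a 0.05 alpha risk and a 0.2 beta risk in a bilateral contrast", and the result is that "20,171 people are needed in each arm, intervention and control groups" "to detect a relative risk of 0.9". On recruitment, "in one and a half years we expect that there will be 54.000 people, 27.000 for each arm".

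Section 2.5.2 (Monitoring and result variables) lists the outcomes. For the primaries it begins: "The study primary outcomes will be hard CHD (myocardial infarction, cardiac revascularization, or coronary death". It then adds MACE (hard CHD plus fatal or nonfatal ischemic stroke), all-cause mortality, and a set of risk-factor variables such as lipids, blood pressure and BMI. The secondary outcomes are CHD (hard CHD plus angina), cerebrovascular disease (ischemic stroke plus TIA), "CVD (a composite of MACE, angina, and transient ischemic attack"), and adverse effects of lipid-lowering drugs. The abstract gives the same primary outcomes.

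Symptomatic PAD is in none of these outcomes. Elsewhere in the Methods it appears only as an exclusion criterion (section 2.2) and in the sizing sentence. No expected rate or power is given for any listed outcome.

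**The concern.** For a fixed relative risk, the power of an event comparison depends on how many events occur. A power figure therefore belongs to one endpoint and its rate. The figure in section 2.3 belongs to an endpoint that the trial does not plan to analyse, while the first study aim is to reduce CHD incidence and all-cause mortality.

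The practical risk lies in interpretation. A null result for hard CHD or MACE could be read as coming from a trial with 80% power to detect a 10% relative reduction, when its actual power for that outcome was never stated and may be much lower. The article gives both the sizing endpoint and the outcome list, and the two do not match, so this is not a detail left to an analysis plan.

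**Working it through.** **1. Endpoint compared with outcomes**

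| Component | Sizing composite (2.3) | Hard CHD (primary) | MACE (primary) | CVD (secondary) |
|---|---|---|---|---|
| MI, revascularization, coronary death | yes, as coronary disease | yes | yes | yes |
| Angina | yes, if coronary disease has its usual meaning | no | no | yes |
| Ischemic stroke | yes, as cerebrovascular disease | no | yes | yes |
| TIA | yes, if cerebrovascular disease has its usual meaning | no | no | yes |
| Symptomatic PAD | yes | no | no | no |

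Section 2.3 does not define coronary or cerebrovascular disease. Even if both are read narrowly, symptomatic PAD separates the composite from every listed outcome. Hard CHD and MACE sit inside the composite, so their rates are lower than 7%. All-cause mortality does not sit inside it, because non-cardiovascular deaths count.

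**2. Reproducing the plan's figure**

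Inputs from section 2.3: p1 = 0.07, p2 = 0.9 × 0.07 = 0.063, two-sided alpha 0.05 (z = 1.960), power 0.80 (z = 0.842).

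n = [1.960·√(2p̄(1−p̄)) + 0.842·√(p1(1−p1) + p2(1−p2))]² / (p1−p2)², with p̄ = 0.0665.

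n = (0.6906 + 0.2965)² / 0.007² = 19,887 per arm.

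With continuity correction, (n/4)·[1 + √(1 + 4/(n·0.007))]² = 20,171 per arm. This matches the stated figure exactly. The arithmetic is sound, and the 80% belongs to the 7% composite.

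Without continuity correction, power for that composite is 80.6% at 20,171 per arm and 90.4% at 27,000.

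**3. Power at lower control rates**

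The document gives no rate for hard CHD, MACE or mortality, so the 3-year control rates below are assumptions. RR is 0.9, individuals are treated as independent, and no continuity correction is used:

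power = Φ{[(p1−p2)·√n − 1.960·√(2p̄(1−p̄))] / √(p1(1−p1) + p2(1−p2))}

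Example at 5% and n = 27,000: (0.8216 − 0.5896) / 0.3008 = 0.771, and Φ(0.771) = 78%.

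| Assumed 3-year control rate | n per arm for 80% | Power at 20,171 | Power at 27,000 |
|---|---|---|---|
| 7% (the composite) | 19,887 | 81% | 90% |
| 6% | 23,437 | 74% | 85% |
| 5% | 28,408 | 66% | 78% |
| 4% | 35,865 | 56% | 68% |
| 3% | 48,292 | 44% | 55% |
| 2% | 73,147 | 31% | 40% |

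**4. Break-even rates**

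Solving the same formula for 80% power gives a control rate of about 6.9% at 20,171 per arm and about 5.25% at 27,000. Since 5.25 / 7 = 0.75, an outcome keeps 80% power at 27,000 per arm if its rate is at least three quarters of the composite's.

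**The case against.** Expected enrolment exceeds the stated requirement: 27,000 per arm against 20,171. That margin takes power for the composite to about 90% and keeps 80% down to a control rate of about 5.25%. This stands. The document does not show that MACE falls below that rate. A population chosen for REGICOR and REASON scores of at least 7% could have a MACE rate near it, since 7% is the entry floor for 10-year coronary risk, not the average, and MACE adds stroke.

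The secondary outcome CVD is also close to the sizing composite. The clear difference is symptomatic PAD, and perhaps non-ischemic stroke. If the unmatched events are no more than about a quarter of the 7%, CVD keeps about 80% power at 27,000 per arm. This stands too, but CVD is secondary and the protocol makes no such claim.

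A reader might infer that every primary outcome has a lower event rate than 7% and is underpowered. The document does not support that. All-cause mortality is not a subset of the composite and its rate is not given, so its power could lie on either side of 80%. Most of the risk-factor primaries are continuous and are not governed by an event-rate calculation.

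None of this supplies the missing link between the stated 80% and a listed outcome.

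**Conclusion.** The point holds in this form: the 80% power in section 2.3 is tied to no outcome in section 2.5.2. For hard CHD and MACE the direction is clear. Their rates are below the composite's, so at 20,171 per arm their power is below the stated 80% under the continuity-corrected formula that reproduces that number. (Without the correction, the threshold is a rate of about 6.9%.)

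The size of the shortfall is not known from the document. Over assumed control rates of 5% down to 2%, power runs from 66% to 31% at 20,171 per arm and from 78% to 40% at 27,000. At the expected enrolment, a shortfall for MACE is possible but not shown, because it requires a rate under about 5.25%.

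These figures assume RR 0.9, 3-year follow-up for everyone and independent individuals. Any design effect from randomizing primary care centers would lower them further.

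**What to change.** Recompute section 2.3 on a listed primary event outcome. MACE is a natural choice because it has more events than hard CHD. Take its 3-year incidence from the eligible EHR population. Then state the power, or the RR detectable with 80% power, at the expected enrolment for MACE, hard CHD and all-cause mortality.

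Making the 7% composite a primary outcome would restore the match on paper but is a less suitable repair. ABI screening takes place in one arm only and may change how PAD is recorded there, which could bias an endpoint that counts PAD.

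The cost is an incidence estimate for each outcome and a rewritten paragraph. The stated power for the cardiovascular primaries will probably look less favourable. No extra patients are needed, since enrolment already takes in the expected flow of eligible people.

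### The sample size is the individually randomised figure with no design effect, although 274 primary care centers are randomised

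*Protocol article*

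**What the plan says.** The design is clustered. Section 2.1 (Study design) says: "This study will be conducted as a pragmatic cluster randomized trial in the primary care centers (PCC) of Catalonia". The Methods paragraph of the abstract gives the number of units: "A total of 274 primary care centers will be randomized into two groups".

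Section 2.3 (Sample size) takes the three-year risk of a cardiovascular event, which "is expected to be 7% in the selected population during a period of 3 years", and sets the error rates: "Accepting a 0.05 alpha risk and a 0.2 beta risk in a bilateral contrast". It concludes that "20,171 people are needed in each arm, intervention and control groups, to detect a relative risk of 0.9".

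The same section forecasts recruitment from about 36,000 eligible people a year: "in one and a half years we expect that there will be 54.000 people, 27.000 for each arm". It mentions no ICC, no number of patients per center, no design effect and no number of centers. It does not link the 27,000 to clustering.

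**The concern.** Patients of one center share staff, workflow and catchment area, so their outcomes are correlated. When centers are randomised, this correlation inflates the variance of the treatment comparison by a factor that grows with the number of patients per center. Here that number is large: about 147 per center at the stated requirement and about 197 at the forecast. At such sizes a small ICC has a visible effect.

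If the calculation ignores this, the trial has less power than stated, and readers will judge a non-significant result against 80% power for a relative risk of 0.9 that the design may not have had.

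**Working it through.** **Inputs.** From section 2.3: control risk 0.07; relative risk 0.9, hence 0.063 in the intervention arm; two-sided alpha 0.05; power 0.80; 20,171 per arm stated as needed; 27,000 per arm expected. From the abstract: 274 centers. Assumed here: an equal split of 137 centers per arm, equal center sizes unless noted, and a range of ICC values, because the article gives none.

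**Step 1: reproduce the stated figure.** With p1 = 0.07, p2 = 0.063 and mean p = 0.0665, the formula for individual randomisation is

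n = [1.960 × √(2p(1−p)) + 0.842 × √(p1(1−p1) + p2(1−p2))]² / (p1 − p2)²

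= (0.6906 + 0.2965)² / 0.007² = 19,886 per arm (unrounded inputs).

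The continuity correction gives

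(n/4) × [1 + √(1 + 4/(n × 0.007))]² = 20,170.9, i.e. 20,171.

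This is an exact match, so the design effect built into the stated number is 1.

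**Step 2: design effect.** DE = 1 + (m − 1) × ICC, where m is patients per center:

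- at 20,171 per arm, m = 40,342/274 = 147.2
- at 27,000 per arm, m = 54,000/274 = 197.1

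**Step 3: power for relative risk 0.9**, from the two-proportion test without continuity correction, at an effective size of N/DE per arm:

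| ICC (assumed) | DE, m = 147 | Power, 20,171 per arm | DE, m = 197 | Power, 27,000 per arm |
|---|---|---|---|---|
| 0 | 1.00 | 80.6% | 1.00 | 90.4% |
| 0.001 | 1.15 | 75.0% | 1.20 | 84.7% |
| 0.002 | 1.29 | 69.9% | 1.39 | 79.0% |
| 0.005 | 1.73 | 57.3% | 1.98 | 64.0% |
| 0.01 | 2.46 | 43.6% | 2.96 | 47.5% |

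**Step 4: how much clustering each size can absorb.**

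- At 20,171 per arm the only slack is the continuity correction: 20,171/19,886 = 1.014, so the largest ICC is 0.0143/146.2, about 0.0001.
- At 27,000 per arm: 27,000/20,171 = 1.339, so the largest ICC is 0.339/196.1 = 0.0017. On the uncorrected base of 19,886 it is 0.0018.
- If center sizes vary with an assumed coefficient of variation (CV) of 0.6, DE = 1 + ((1 + CV²)m − 1) × ICC, and the limit falls to 0.339/(1.36 × 197.1 − 1) = 0.0013.

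**Step 5: can more patients per center make up the loss?** With k = 137 centers per arm fixed, the number needed per arm is n × k × (1 − ICC)/(k − n × ICC).

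- With n = 20,171 and ICC 0.005: 20,171 × 137 × 0.995/(137 − 100.9), about 76,000 per arm (about 72,000 on the uncorrected base).
- Once ICC exceeds 137/20,171 = 0.0068 the denominator is negative, and no number of patients in these centers reaches 80%.

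**Step 6: detectable effect.** At 27,000 per arm and ICC 0.005 the effective size is 27,000/1.98 = 13,634 per arm. Solving the Step 1 formula for 80% power gives a relative risk of about 0.88.

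**The case against.** The strongest reply is that the trial expects 27,000 per arm, not 20,171, and that this surplus of about 34% may be enough. With equal centers it keeps 80% power up to an ICC of about 0.0017. At a 7% risk that corresponds to a between-center standard deviation of √(0.0017 × 0.07 × 0.93), about 1.05 percentage points, or center risks of roughly 4.9% to 9.1% (two standard deviations either way), which is not obviously a small spread. Eligibility is also narrow (section 2.2: age 50 to 74, both risk scores at least 7%, no previous coronary disease or stroke), which may reduce differences between centers. The deprivation index and provider quality standards listed in section 2.5.2 might explain part of what remains. Even at ICC 0.005 the detectable relative risk moves only from 0.90 to about 0.88.

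Much of this stands. Without an ICC, a shortfall at 27,000 per arm is possible but not shown, and the losses at 0.005 and 0.01 are illustrations rather than predictions. The basis also changes within the working: the power figures use the uncorrected test, while the limits use the corrected 20,171. The differences are small, as Step 4 and Step 5 show.

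None of it rescues the stated requirement. The 27,000 is a recruitment forecast that the article does not tie to clustering. Nor can the brevity of a journal article explain the gap: the published number equals the unclustered answer, so no unreported design effect can be inside it.

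**Conclusion.** The concern holds. As a statement of what this cluster trial needs, 20,171 per arm is wrong: it gives 80% power only if the ICC is about 0.0001 or less, and 75% at 0.001 or 57% at 0.005. That must be corrected whatever the true ICC.

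Whether the expected 54,000 patients are enough is an open question that the article does not address. They are enough if the ICC is at most about 0.0017 with equal center sizes (about 0.0013 at a size CV of 0.6), and not enough above that. These limits assume 137 centers per arm, the article's 7% risk and relative risk of 0.9, and an analysis that takes the clustering into account.

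**What to change.** Rewrite section 2.3 for the design actually used:

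1. Estimate the ICC for the primary outcome, and the CV of the number of eligible patients per center, from the existing primary care records.
2. Apply DE = 1 + ((1 + CV²)m − 1) × ICC, with m the mean number of patients per center.
3. State the power for a relative risk of 0.9, and the relative risk detectable with 80% power, for 274 centers and about 54,000 patients, over a short range of ICC values around the estimate.
4. Either drop 20,171 as the requirement or label it as the figure before allowance for clustering, and say whether 27,000 per arm is sufficient.

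The cost is one query on data already held and one rewritten paragraph. Enrolment and the intervention do not change. The price is that the stated power or detectable effect may look less favourable than it does now.
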